## Abstract

The aim of this article is to present the research protocol for a prospective cohort study that will assess the olfactory function and the effect of an intervention based on olfactory training in healthy very old adults (≥75 years old). A convenience sample of 180 older people (50% female) will be recruited in three different environments: hospitalized control group (CH) with stable acute illness (*n* = 60); ambulatory control group (CA) of community-based living (*n* = 60); and an experimental odor training group (EOT) from nursing homes (*n* = 60). The odor training (OT) intervention will last 12 weeks. All the volunteers will be assessed at baseline; CA and EOT groups will also be assessed after 12 weeks. The primary end point will be change in olfactory capacity from baseline to 12 weeks period of intervention or control. The intervention effects will be assessed with the overall score achieved in Sniffin Sticks Test (SST) – Threshold, Discrimination, and Identification (TDI) extended version. Secondary end points will be changes in cognitive tasks, quality of life, mood, immune status, and functional capacity. All these measurements will be complemented with an immune fitness characterization and a deep proteome profiling of the olfactory epithelium (OE) cultured *ex vivo*. The current study will provide additional evidence to support the implementation of olfactory precision medicine and the development of immunomodulatory nasal therapies based on non-invasive procedures. The proposed intervention will also intend to increase the knowledge about the olfactory function in very elderly people, improve function and quality of life, and promote the recovery of the health.

## Introduction

Europe is aging. In 2050, more than 28% of the population will be over the age of 65 (United Nations, 2019). The continuous declining of birth rates and the increasing of life expectancy are converting European regions into increasingly aging area. Neurodegenerative diseases (ND) are a significant portion of neurological disorders and these already account for 1/3 of the cost of illness in Europe furthermore social and economic burden will continue to increase as the population ages (Deuschl et al., 2020). Addressing the human and economic challenge of aging and neurodegenerative diseases requires clinical and research tools that facilitate precision medicine. We need disruptive approaches that generate innovative tools for early detection and diagnosis of ND and non-invasive interventions to slow and/or stop its progression in women and men, highlighting their differences if any, and incorporating a gender perspective in the solutions.

The olfactory function is responsible for detecting and processing odors, and is one of the oldest and most important senses for living organisms (Delgado-Losada et al., 2020). The sense of smell provides important information about the air we breathe, the foods we eat and alert us to dangers in the environment (Schiffman, 1997; Hadley et al., 2004; Schriever et al., 2014). Beyond the risks that the smell loss may entail for older people, moreover the consequent reduction in quality of life, the olfactory dysfunction may be an important early indicator of ND such as Parkinson’s and Alzheimer’s (Djordjevic et al., 2008; Haehner et al., 2013; Knudsen et al., 2015; Doty, 2017; Marin et al., 2018; Kondo et al., 2020), as well as COVID-19 (Moein et al., 2020; Sedaghat et al., 2020). In addition, olfactory system dysfunctions have been found in other neurological disorders such us schizophrenia, or depression (Sanna et al., 2021) ultimately related to alterations of the immune system, suggesting that olfactory system abnormalities may be also associated with the immune system (reviewed in Strous and Shoenfeld, 2006). During the last years, olfactory proteomics has been postulated as a powerful approach to characterize global proteome dynamics in order to unravel the modulation of cell-signaling networks during odor processing (Lachén-Montes et al., 2016), as well as during the neurodegenerative process (Lachén-Montes et al., 2017, 2019a,b, 2020a).

In the literature, there is a full consensus stating that sense of smell gradually decreases with age, especially after the age of 60 (Doty et al., 1984; Murphy et al., 2002; Doty et al., 2011; Mullol et al., 2012; Hummel, 2014; Sorokowska et al., 2015; Masala et al., 2018; Doty, 2019; Kondo et al., 2020). In relation to sex differences, by one side Doty et al. (1984) have observed that women outperformed men at all ages in healthy subjects, and a recent meta-analysis has confirmed the female olfactory superiority, although authors emphasized the effect sizes observed were notably small (Sorokowski et al., 2019). By other side, when comparing healthy control subjects with Parkinson’s disease patients, new findings (Melis et al., 2019; Solla et al., 2020) have remarked the importance of sex effect analysis. Regarding smoking, there is no consensus indicating that it accelerates olfactory dysfunction (Vennemann et al., 2008; Fjaeldstad et al., 2021). However, there is evidence that current smoking, but not former smoking, was associated with posttraumatic olfactory loss; namely, a history of smoking was not associated to impairment of olfactory function (Vennemann et al., 2008). Related to lifestyle and behavior factors, the regular exercise was associated with a lower 10-year cumulative incidence of olfactory impairment; in addition, the association with exercise was more robust among those who exercised three or more times per week than among those who only exercised 1–2 times per week (Schubert et al., 2013).

Training and repeated exposure to odorants leads to enhanced olfactory sensitivity (Al Aïn et al., 2019). The olfactory or odor training (OT) is a non-invasive technique with no significant side effects. Previous studies have proven the usefulness of OT in handling olfactory deficits with various etiologies (Hummel et al., 2009; Patel, 2016; Pekala et al., 2016; Al Aïn et al., 2019). The OT may be considered a simple protocol, which has proven efficacy in some patients with olfactory dysfunction. Despite increasing acceptance as an appropriate intervention, questions related to both efficacy and mechanism of action have persisted (Hummel et al., 2009; Turner, 2020).

In non-expert individuals with a normal sense of smell, a short-term OT improves olfactory performance (Dalton et al., 2002), and repeated exposure to an odorant enhances odor detection (Engen, 1960; Doty et al., 1981; Rabin and Cain, 1986; Dalton et al., 2002). Along the same lines, a few seconds of OT daily is considered as a behavioral therapy in patients with olfactory dysfunction (Abolmaali et al., 2002; Mueller et al., 2005; Rombaux et al., 2006; Hummel et al., 2009; Fleiner et al., 2012; Haehner et al., 2013; Konstantinidis et al., 2013; Damm et al., 2014; Schriever et al., 2014; Al Aïn et al., 2019). There is evidence that OT may increase olfactory sensitivity in Parkinson’s disease (Haehner et al., 2013). Notably, it has been also shown in animal models that odor training may have an impact on their cognitive functions (Lasarte-Cia et al., 2018). Finally, the evidence about OT in healthy older population and its efficacy is scarce (Schriever et al., 2014; Birte-Antina et al., 2018). Table 1 shows a brief survey of OT protocols found in the literature.

**TABLE 1 T1:** Review of odor training protocols.

References	Study type Sample etiology	Sample (Mean age ± SD)	Test	Methods	Results
Al Aïn et al. (2019)	Randomized controlled trial Healthy population	*N* = 36 (24; 18–35) 58% ♀ Exp1 (OT) = 12 Exp2 (VCT) = 12 Con = 12	SST; UPSIT	Exp1(OT) = 6 weeks 1/day Intensive training (20’) Exp2(VCT) = visual control training Con = no training	Intensive OT can improve olfactory function. Improvement is associated with changes in the structure of olfactory processing areas of the brain.
Birte-Antina et al., 2018	Controlled, unblinded, longitudinal study Older people with normal olfactory function (>27/28 points in TDI score)	*N* = 91 78% ♀ 50–84 (61.1, ± 8.7) Exp(OT) = 60 Con = 31	SST	Exp(OT) = 20 weeks, 2/day 4 odors Con = Sudoku tasks	Positive effect of OT in older people on olfactory function, which extended to general mood and depressive symptoms. For cognitive function, a positive effect on verbal fluency was observed, but no effect on short-term memory or attentiveness.
Fornazieri et al. (2019)	Prospective Postinfectious, posttraumatic, or idiopathic olfactory loss	*N* = 25 68% ♀ (22–82 y) Exp1(classical training) = 12 Exp2(modified training) = 13	UPSIT	12- and 24-weeks testing 2/day for 24 months (10’ each) Exp1 = 4 odors Exp2 = 8 commercial products	Adherence rate of the patients after 3 months was 88% and after 6 months was 56%.
Gudziol et al. (2006)	Longitudinal Impairment of olfactory sensitivity (hyposmia or functionally anosmia)	*N* = 83 58% ♀ 12–84 y (58.2 ± 11.8)	SST	No intervention, olfactory testing was performing in two occasions (mean interval 136 days (7 days – 6.7 years)	Logistic regression showed that more than 60% of the subjects reported an improvement of olfactory sensitivity when the TDI score increased by 5.5 points. There is a statistically significant relation between measured and perceived improvement of olfactory function in patients who first presented with the diagnosis of anosmia or hyposmia.
Haehner et al. (2013)	Prospective, controlled nonblinded study Parkinson disease	*N* = 70 35% ♀ Exp(OT) = 35 (63.1 ± 8.3) Con = 35 (61.5 ± 9.5)	SST; threshold tests for the odors used in the training process	Exp(OT) = 12 weeks 2/day 4 odors (10” each) Con = no training	Significant increase in Exp group; and no changes in Con Group
Hummel et al. (2009)	Prospective Patients with olfactory dysfunction	*N* = 56 59% ♀ Exp(OT) = 40 (56 ± 11) Con = 16 (62.3 ± 13.4)	SST; threshold tests for the odors used in the training process	Exp(OT) = 12 weeks 2/day 4 odors (10” each) Con = no training	Positive significant increase in Exp group; and no changes in Con Group
Pekala et al. (2016)	Systematic review Olfactory loss Multiple etiologies		SST (6 out 10)		Statistically significant improvement (the mean difference in post treatment TDI score between groups was < 4 points.
Schriever et al. (2014)	Prospective Older people	*N* = 91 70% ♀ 55–96 (81 ± 8.6) Exp(OT) = 23 Con = 48	Odor identification and PEA threshold (SST)	Exp = 12 weeks 2/day 4 odors (30” each) Con = no training	No significant increase in olfactory function was observed in the training group.

*Exp, experimental group; Con, control group; SST, sniffin sticks test; TDI, threshold, discrimination and identification; UPSIT, university of Pennsylvania smell identification test; y, years old.*

Although there are important findings showing that intensive OT can improve olfactory function and in addition, this improvement is associated with changes in the structure of olfactory processing areas of the brain (Al Aïn et al., 2019). More research is needed to establish the optimal protocols i.e., quantity of odorants, training duration, associated-molecular events, and the target patient population most likely to improve using this technique (Patel, 2016). Therefore, the aim of this pilot study is to examine the effects of a well-controlled and semi supervised 12-weeks OT on olfactory function, OT-associated OE proteostatic changes, cognitive, immune and functional status, and quality of life in very elderly adults.

## Materials and Methods

### Study Design and Participants

The sample is a convenience sample and is composed by three groups (*N* = 180, 50% females). Sixty hospitalized patients with acute illness (hospitalized control group – CH), sixty ambulatory patients from the community (ambulatory control group – CA) and, sixty from nursing home – the experimental odor training group (EOT). The study follow the principles of the Declaration of Helsinki (World Medical Association, 2013) and was approved by the Complejo Hospitalario de Navarra Clinical Research Ethics Committee on October 21, 2020 (PI_2020/113). All volunteers or their legal representatives will be asked to sign a written informed consent form, also approved in advance by the ethics committee. There will be no financial compensation.

Following the literature procedures (Delgado-Losada et al., 2020) all the volunteers will be previously evaluated by an expert otolaryngologist including anamnesis and nasal endoscopic examination to exclude the possibility of an otorhinolaryngology alteration or pathology that may modify the results of the olfactory test. Therefore, sinusitis, prior nasal surgery, nasal polyps, presence of nasal congestion at the moment of test administration or recent upper respiratory tract infection within two weeks, medication intake with repercussion in olfactory performance or to have reported COVID-19 compatible smell symptomatology are exclusion criteria.

The inclusion criteria are: (i) ≥ 75 years old; (ii) compliance with testing procedure; (iii) Mini-Mental State Examination (MMSE) equal to or greater than 21 points (Pi et al., 1994; Ostrosky-Solís et al., 2000; Reyes-de-Beaman et al., 2004); (iv) Barthel index ≥ 60; (v) participants from acute hospitalized group must be clinically stable. The exclusion criteria are positive diagnosis of any kind of neurodegenerative disease and/or nasosinusal pathology (described before).

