### Data Analysis

Demographic and outcome data will be summarized for the whole sample and for each group using mean and standard deviation or median and interquartile range for continuous variables and via frequencies and percentages for categorical ones. For the CH group only a descriptive characterization of the measured variables will be performed. In the CA and EOT groups, baseline data will be compared using t-test or Mann-Whitney U test for continuous variables and with chi-square test and Fisher test for categorical ones. For each group, within group pre-post differences will be computed using t-test for dependent samples or Wilcoxon rank sum test. Linear models will be computed in order to compare outcome data between groups, adjusting by baseline outcome data and also by the variables that showed baseline differences.

Further, the association between olfactory level measured with TDI score and marked OE protein modifications (based on fold-change), cognitive, neurological, functional, mood status and quality of life will be analyzed using Pearson or Spearman correlation coefficients. All significant, nearly significant, clinically relevant or potentially confounding variables will be considered in a multiple linear regression model with TDI as dependent variable. In this global model non-significant variables will be removed, which, when eliminated, do not change the estimators of the effect of the rest of the variables in the model. The biochemical analysis, the immune information of each subject and the data associated with pharmacological treatments, fragility, cognition, will also be correlated with olfactory level, with the aim of testing the precision olfactory medicine as a useful tool in the day-to-day context of the Geriatrics Unit. To exclude the effect of sex and age, correlations will be performed as partial correlations, including sex and age as covariates. The statistical analysis will be performed with SPSS (version 26; SPSS Inc., Chicago, IL, United States).

Sample size was calculated based on previous literature (Hummel et al., 2009) on the effects of OT on olfactory function, a medium effect size (*d* = 0.5) and a standard deviation of the outcome of *SD* = 0.8 were assumed (Birte-Antina et al., 2018).

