### Intervention

#### Control

The control group will be composed by sixty ambulatory patients from the community (CA). This group will undergo a complete assessment at baseline and after 12 weeks. The volunteers of CA group will receive usual health care assistance; therefore they will not participate in any kind of olfactory training.

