#### Training Protocol

The experimental odor training group (EOT) will be composed by sixty older adults from nursing home. This group will undergo a complete assessment at baseline and after 12 weeks. The training intervention will be performed over a period of 12 weeks and will involve patients exposing themselves once daily to 4 different scents of the four commonly used odors during 20 s each (phenyl ethyl alcohol (PEA): rose, eucalyptol: eucalyptus, citronellal: lemon, and eugenol: cloves). These four odorants were chosen to be representative of four odor categories that tried to identify/represent primary odors (Amoore, 1977; Haehner et al., 2013). These categories are flowery (e.g., rose), foul, fruity (e.g., lemon), aromatic (e.g., cloves), burnt, and resinous (e.g., eucalyptus). Training patients received four vial topaz (total volume 5 ml) with one of the four odors in each (1 ml each, soaked in cotton pads to prevent spilling). All vials will be labeled with the odor name. Patients will be asked to sniff the odors in the morning for approximately 20 s each. Participants will be asked to refrain from smoking, eating, or drinking (except water) during the hour prior to training and testing (Al Aïn et al., 2019). Figure 2 shows a summary outline of the proposed protocol.

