**FIGURE 2 F2:**
[figure not shown]
Odor training protocol (own elaboration).

Adherence to the OT intervention will be documented in an *Odor training diary* (P.R.O-V1.1E, 2020). By one side, some protocols in literature (Table 1) performed the training sessions twice a day or 12 weeks of OT (Hummel et al., 2009; Haehner et al., 2013; Schriever et al., 2014; Fornazieri et al., 2019). However, by other side, Schriever et al. (2014) and Fornazieri et al. (2019) have indicated that only half part of the sample strictly follow the protocol. In this regard, our main objective is to propose a protocol that can be followed in an easy and manageable way by our sample of very old adults. For this reason, we propose only one training session per day during a 12 weeks period. In the same way, seems important to highlight that at least once a week a researcher of our staff will supervise the training sessions and furthermore participants will receive a follow up call per week. Lastly, participants who do not experience a subjective perceived improvement in olfactory function tend to lose motivation, so there will be an intermediate smell test with SST at 6 weeks to assess objectively the evolution of performance.

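### Training is completely aliased with care setting (all trained participants in nursing homes, all followed-up controls in the community), so the EOT–CA contrast cannot be read as the effect of odor training

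*Protocol article*

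**What the plan says.** Study Design and Participants describes recruitment without random allocation: "The sample is a convenience sample and is composed by three groups". Apart from the hospitalised patients, these are "sixty ambulatory patients from the community (ambulatory control group – CA) and, sixty from nursing home – the experimental odor training group (EOT"). In the Abstract each group is tied to a place; participants "will be recruited in three different environments: hospitalized control group (CH) with stable acute illness", with the ambulatory group drawn from the community and the trained group from nursing homes. The Intervention section repeats this for each group: "The control group will be composed by sixty ambulatory patients from the community (CA") and "The experimental odor training group (EOT) will be composed by sixty older adults from nursing home". The controls have usual care and no olfactory training.

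Only these two groups have a 12-week assessment. For the hospitalised group, Data Analysis plans description only.

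The Introduction states the purpose in terms of effect: "the aim of this pilot study is to examine the effects of a well-controlled and semi supervised 12-weeks OT on olfactory function". The primary endpoint in the Abstract is the change in olfactory capacity over 12 weeks.

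Data Analysis plans baseline comparisons of the two followed-up groups, pre-post tests within each group, and a between-group model: "Linear models will be computed in order to compare outcome data between groups", adjusted for the baseline outcome and for variables found to differ at baseline.

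Under Training Protocol, contact with trained participants is weekly or more frequent: "a researcher of our staff will supervise the training sessions and furthermore participants will receive a follow up call per week". An intermediate smell test at 6 weeks is also described there. The Control section lists assessments at baseline and 12 weeks only.

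**The concern.** A between-group comparison estimates a training effect only if the untrained group shows what would have happened to the trained group without training. Here the untrained group lives in a different setting. If olfactory scores drift differently over 12 weeks in nursing homes and in the community, for whatever reason, the whole of that difference enters the estimate and looks like a training effect, or hides one.

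The article itself shows how much the comparator's course can matter. Expected Results describes an earlier 12-week study in older people in which the between-group difference appeared because trained participants rose while controls fell below baseline. The change within the trained group alone was not significant. When the comparator's movement contributes to the result, it matters that the comparator comes from the same setting.

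The same aliasing reaches the secondary outcomes and the proteomics. The proteomic comparison is restricted to these two groups, and Expected Results anticipates that it will reveal molecular mechanisms set off by the training.

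**Working it through.** **1. Which cells are observed at 12 weeks** (Abstract; Study Design and Participants; Control; Training Protocol)

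| | Nursing home | Community | Hospital |
|---|---|---|---|
| Trained | 60 (EOT) | none | none |
| Untrained | none | 60 (CA) | none (60 seen at baseline only) |

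**2. What the linear model can estimate.** Write the 12-week change as α + τT + σS + error, with T = 1 if trained and S = 1 if in a nursing home. For all 120 people T = S, so the model reduces to α + (τ + σ)T. Only the sum τ + σ is estimable. As a check, a design matrix with intercept, training, setting and one covariate for 60 + 60 people has 4 columns but rank 3. Adding covariates does not restore the missing rank. They help only as far as measured characteristics account for σ.

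**3. What the pre-post tests can estimate.** Within EOT, setting is constant, but the mean change is training plus retest, time and institutional effects. No untrained nursing-home group is available to subtract those. Differences between settings that stay constant over 12 weeks cancel in within-person change. What remains is a setting-specific change.

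**4. Illustration of size.** The documents give no setting-related drift. Assumptions: true training effect 0; setting difference b in mean 12-week TDI change; SD of change 4 to 5 points; n = 60 per group; two-sided 5%; two-sample t-test.

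Standard error = SD × √(2/60) = SD × 0.1826. Standardised shift = b / SE. The rejection rate is the power of the t-test at that shift.

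| b (points) | SD | SE | b / SE | Rejection rate |
|---|---|---|---|---|
| 0 | any | – | 0 | 5% |
| 1 | 4 | 0.730 | 1.369 | 27.4% |
| 1 | 5 | 0.913 | 1.095 | 19.2% |
| 2 | 4 | 0.730 | 2.739 | 77.5% |
| 2 | 5 | 0.913 | 2.191 | 58.4% |

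The only SD in the article is 0.8, given in the sample-size statement without a unit. If it were in TDI points, b = 1 would be 1/0.8 = 1.25 SD, with a shift of 1.25/0.1826 = 6.85 and rejection above 99%. The SD of 4 to 5 is therefore the milder assumption.

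**5. Link to the planned effect size.** The article assumes d = 0.5. At 60 per group, a training effect of that size is detected with 77.5% power. A setting effect of 0.5 SD with no training effect is declared significant equally often, because the data cannot tell them apart. Alpha, power and dropout are not stated, so the figure of 60 can be neither reproduced nor refuted. The point does not depend on it.

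**6. The same people with training allocated within setting.** With 30 trained and 30 untrained in each setting, intercept, training and setting give 3 columns and rank 3, so τ and σ are both estimable. The variance factor for τ is 1/60 + 1/60 = 0.0333, the same as for 60 versus 60 in the present design. No precision is lost on the overall training effect.

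**The case against.** The other side has several good arguments.

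- **The study does not claim to be randomised.** It calls itself a prospective cohort and a pilot with a convenience sample, and one aim is simply to assess olfactory function in the very old. That aim is untouched, so a reader who concludes that the study answers nothing goes too far. But the Introduction's aim, the primary endpoint and the expected results all concern the effect of training, and the labels do not change that question.
- **The adjective well-controlled.** A reader might take it as a claim about the comparison. In the sentence it qualifies the training, together with semi supervised, so it is no evidence of a false claim about the control group.
- **Known differences between settings.** It is tempting to say that diet, activity, infections, medication and frailty all differ. The article documents none of this. The common criteria (age 75 or over, MMSE at least 21, Barthel at least 60, nasal endoscopy, exclusion of neurodegenerative disease, recent respiratory infection and medication affecting smell) narrow several of them. They do not remove the aliasing.
- **The error rates.** They are correct arithmetic on chosen inputs and show what would follow from a drift, not that there is one. One point is also well below the 6 points that the article treats as a significant change. However, the planned test asks whether the mean difference is zero, not whether it reaches 6.
- **Contact and supervision.** These go to trained participants only, and allocation within setting would not change that. They can fairly be regarded as part of the semi-supervised intervention under test.

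**Conclusion.** The point stands as a structural one. With every trained participant in a nursing home and every followed-up control in the community, the planned between-group models estimate training plus setting. The within-group tests have no untrained nursing-home reference. Screening and adjustment reduce the problem without solving it, and a fuller analysis plan could not solve it, because the group definitions cause it.

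This conclusion needs no numerical assumption. The 19–27% for a 1-point drift rests on an assumed drift, an assumed SD of 4 to 5 and no training effect, and is an illustration only. The documents do not support the stronger inference that the result will in fact be biased, or in which direction. What they do support is that an EOT–CA difference in TDI, secondary outcomes or proteome cannot be assigned to training.

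**What to change.** **Preferred.** Keep the same 120 people and allocate training at random within each setting: 30 trained and 30 untrained nursing-home residents, 30 trained and 30 untrained community-dwellers, stratified by sex. Include setting in the linear model. The totals stay at 60 trained and 60 untrained, and the hospitalised group is not affected.

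The cost is an amendment, a randomisation list, supervision of some training in the community, and possible contamination between trained and untrained residents of one home. The effect estimated is then that of the semi-supervised package, including weekly supervision and calls, and the article should say so.

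**If allocation can no longer be changed.** State in the aims, Data Analysis and Expected Results that the comparison is between trained nursing-home residents and untrained community-dwellers, and that differences in TDI, secondary outcomes and proteome will not be attributed causally to training. This costs wording only, but gives up the causal question.
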